**Visit 1 = Screening (Day -1)**

After signing the informed consent form the inclusion and exclusion criteria are verified. If the criteria are fulfilled the patient will be enrolled in the study.

During this visit the following procedures will be performed:

- Vital signs
- Physical examination
- MFM scale
- 6MWT
- muscle force of knee extension and elbow flexion using hand held dynamometry
- 10 m within 10 s walking test

**Visit 2 = Baseline (Week 0)**

During this visit the following procedures will be performed:

- check inclusion/exclusion criteria
- vital signs
- physical examination
- MRI
- Adverse events
- laboratory
- dispensing of study medication

If the patient still qualifies for the study, he/she will be randomized and receive study medication.

**Visit 3 (Week 13,  $\pm 7$  days)**

During this visit the following procedures will be performed:

- vital signs
- physical examination
- MFM scale
- 6MWT
- muscle force of knee extension and elbow flexion using hand held dynamometry
- 10 m within 10 s walking test

- Adverse events
- laboratory
- dispensing of study medication
- collection of study medication

**Visit 4 = End of Study Visit (Week 26,  $\pm 7$  days)**

During this visit the following procedures will be performed:

- vital signs
- physical examination
- MFM scale
- 6MWT
- muscle force of knee extension and elbow flexion using hand held dynamometry
- 10 m within 10 s walking test
- MRI
- Adverse events
- laboratory
- collection of study medication

Patients (or their parents) can voluntarily withdraw from the study at any time. However, the investigator should try to assess the main reason and capture this information in the CRF.

In case of screening failure due to exclusion criteria the patient can be re-screened once for this study.

**4.2.1 Healthy volunteers**

10–20 age matched healthy boys within the same age range and 10 – 20 healthy male controls will be enrolled to obtain normal values of mitochondrial and muscle metabolism. All healthy controls will be seen at two time points (screening and for blood drawing). Healthy children (and their caregivers) will be asked to participate in our study while undergoing an elective surgery at our hospital. By this blood drawing will be done as part of the routine safety protocol while the child is already under anaesthesia. An additional amount of 4 ml of blood will be drawn for this study but no additional venous puncture will be necessary for this study.

Healthy adult controls will be identified for potential recruitment using IEC/IRB approved newspaper advertisements, mailing lists, websites or database available at UKBB/USB.

**Visit 1 = Screening**

After signing the informed consent form the inclusion and exclusion criteria are verified. If the criteria are fulfilled the patient will be enrolled in the study.

**Visit 2 = Baseline**

During this visit the following procedures will be performed:

- check inclusion/exclusion criteria
- blood drawing

**4.2.2 Criteria for stopping the study**

The following conditions/events can lead to an early termination of the study:

- withdrawal of consent
- protocol violations caused by the patients (noncompliance)
- logistical reasons (relocation of patient etc.)
- circumstances which do not permit any more regular visits in the context of the study
- abnormal laboratory values, including liver or renal function tests (transaminasis  $>2 \times$  ULN, creatinine  $>2 \times$  ULN)
- abnormal increase in blood pressure as determined by the investigator
- For safety of the patient as considered by the investigator

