**4.2.3 Conditions for unblinding**

Unblinding is the process by which the allocation code is broken so that the investigator, clinical staff and/or the trial statistician becomes aware of the intervention for a person participating in a trial. The usual reason for unblinding is that a person participating in the study has encountered an urgent medical problem necessitating that the clinician know his/her intervention allocation. The principal investigator assess the need for unblinding where a serious adverse event has occurred and the treatment or allocation code is required in order to enable clinical treatments to

be planned. Upon unblinding, the site personnel will record the participant withdrawal and allocation in the person's clinical and trial notes along with the appropriate clinical notations.

**Unblinding envelopes:** A series of envelopes, each labelled with the randomisation number that contain the allocation for that person. These envelopes are sealed by the central randomisation service, and are only opened if emergency unblinding is required.

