## **7. SAFETY**

### **7.1 Safety parameter: measuring methods and time**

At every study visit a clinical examination will be performed and the vital parameters blood pressure and heart rate will be measured. The assessment of blood chemistry and of the following parameters is foreseen at every visit (respectively visit 1 or 2):

- full blood count, as with the intake of metformin in the context of the registration trials isolated cases of leucopenia, thrombopenia, and haemolytic anaemia were observed
- clinical chemistry (transaminasis, creatinine, electrolytes, urea),
- marker of the muscle necrosis (creatine kinase concentration),
- makers of oxidative stress: (8OHdG urine concentrations, carbonylated preteins and 4-HNE serum concentration)
- markers of nitrosative stress (nitrotyrosin, plasma; ADMA; serum; cGMP, urine)
- all amino acids
- glucose metabolism marker (HbA1c)
- lipid metabolism marker (cholesterol, HDL, LDL, triglycerides)

The intake of metformin has to be stopped in case of clinically significant changes (increase of creatinine and transaminasis  $>2 \times \text{ULN}$ )

If pathologic changes independent of the known muscle disease should be detected, the affected patients will be informed immediately and the possibilities of further investigation, respectively treatment of these abnormalities according to current medical knowledge will be discussed.

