### **8.6 Definition of the evaluation groups**

Intention-to-treat (ITT) analysis

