### **9.2 Final examination in case of premature withdrawal from the trial**

In this case it is necessary to perform a final medical examination for the safety of the child (patient group). The following procedures will be performed:

- vital signs
- physical examination
- MFM scale, 6MWT, 10 m within 10 s walking test, muscle force of knee extension and elbow flexion using hand held dynamometry
- MRI
- Adverse events
- laboratory
- collection of study medication

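### Stopping study medication is not separated from leaving the study, so an earlier MFM D1 value can replace an obtainable week-26 outcome in the ITT analysis

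*Protocol*

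**What the plan says.** **Grounds for termination.** Section 4.2.2 is headed as criteria for stopping the study, but its items concern single patients. It opens: "The following conditions/events can lead to an early termination of the study". The list puts "protocol violations caused by the patients (noncompliance" and "abnormal laboratory values, including liver or renal function tests" (transaminases or creatinine above 2 x ULN) beside withdrawal of consent, relocation and the investigator's judgement on safety.

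**Unblinding.** Section 4.2.3: "Upon unblinding, the site personnel will record the participant withdrawal and allocation". The sealed envelopes are reserved for emergencies.

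**After an early exit.** Section 9.2: "In this case it is necessary to perform a final medical examination for the safety of the child (patient group". The examination includes the MFM, 6MWT, dynamometry and MRI. No section describes a further visit. Section 11.3 says that data collected up to withdrawal are used, and section 4.3 says that drop-outs after randomisation are not replaced.

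**Analysis.** The primary endpoint is the change in MFM D1 from baseline to week 26 (4.1, 8.1). Section 8.5 specifies last observation carried forward. Section 8.6 says only "Intention-to-treat (ITT) analysis".

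**Laboratory rule stated a second time.** Section 7.1: "The intake of metformin has to be stopped in case of clinically significant changes", which it describes as an increase of creatinine and transaminases above 2 x ULN.

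**The concern.** An intention-to-treat comparison is most credible when the outcome is measured at the planned time in every randomised boy, whatever treatment he took. Here three events that may be connected with treatment (poor compliance, abnormal laboratory values, a broken code) can end, or in the case of unblinding are recorded as ending, a boy's participation. Many such boys could still attend the week-26 visit. For them the endpoint becomes an earlier measurement labelled as week 26.

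In a disease that section 4.1 describes as losing 17.2% per year on D1, an earlier value generally looks better than the later one would have. If exits differ between arms in number or timing, the comparison shifts for reasons unrelated to efficacy. The protocol creates this imputation itself and could avoid it. Because the wording of 4.2.2 is permissive, two boys with the same trigger may also be handled differently.

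**Working it through.** **1. The plan's own figures (8.2, pilot table in 3.1.1).**
- Placebo change: -17.2/54 x 16 = -5.10. Verum change: +6.1. Planned difference: 6.1 + 5.10 = 11.2 points.
- SD of change: 11.6. Two-sided alpha of 0.05 is assumed, since sidedness is not stated.
- A simulated two-group rank-sum test (20,000 runs, normally distributed changes) gives power 0.79 at 19 per arm, so the 38 complete datasets reproduce closely.
- 38/0.9 = 42.2, which agrees with about 42 recruited. The plan therefore expects about 42 - 38 = 4 boys without complete data. It does not split them by cause.

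**2. Following one boy through the text.** A boy is non-compliant, or his transaminases exceed 2 x ULN, at the week-13 visit.
- 4.2.2: his participation may be ended.
- 9.2: he has a final examination, including MFM.
- No later section asks for a week-26 assessment.
- 8.5: the week-13 D1 value becomes his week-26 value.
- 8.6: he is analysed in his allocated arm with that value.

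For a boy whose code is broken the path is the same, except that 4.2.3 takes his withdrawal for granted.

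**3. Size for one boy.** Assumptions not in the protocol: linear decline, 17.2 points per 52 weeks, 21 boys per arm, and the boy would have gone on declining.
- Decline by week 26: 17.2 x 26/52 = 8.6 points.
- Unobserved after week 13: 17.2 x 13/52 = 4.3 points.
- Effect on the arm mean: 4.3/21 = 0.20 points, and 0.20/11.2 = 1.8% of the planned difference.
- With the plan's 54-week year: 17.2 x 13/54 = 4.1 points, and 4.1/21 = 0.20.

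**4. Range, if all four expected losses fell in one arm.**
- Week-13 values carried: 4 x 4.3/21 = 0.82 points (0.82/11.2 = 7%).
- Baseline values carried: 4 x 8.6/21 = 1.64 points (1.64/11.2 = 15%). This is extreme, because 9.2 asks for an MFM at exit.

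The 11.2 points refer to 16 weeks and the shifts to week 26, so the percentages only show scale.

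**5. Direction.** If a boy would have declined, carrying forward flatters his arm. If a verum boy would have kept improving at the pilot rate, 6.1 x 13/16 = 5.0 points of gain would be lost, or 5.0/21 = 0.24 against verum. That is also an assumption, since he may be off treatment. The sign is not fixed by the documents.

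**6. Laboratory rule, side by side.**

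| | 4.2.2 | 7.1 |
|---|---|---|
| Trigger | transaminases and creatinine listed as separate items, each above 2 x ULN | creatinine and transaminases named together, above 2 x ULN |
| Force | may follow | has to follow |
| Consequence | early termination | metformin intake stops |
| L-citrulline and follow-up | not separated from termination | not mentioned |

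**The case against.** **Formal conflict with ITT.** A reader might infer that these boys are removed and that 8.6 is contradicted. The documents do not support that. The wording of 4.2.2 permits termination without requiring it; only 4.2.3 presupposes withdrawal. The MFM is measured at the exit examination, 11.3 retains data collected up to withdrawal, and carrying forward lets every randomised boy with a baseline stay in his allocated arm. This objection stands against the word contradiction. It leaves the weakness that an imputed value replaces one that could have been measured.

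**Bias towards verum.** Section 2.2 mentions gastrointestinal symptoms at the start of metformin, so a reader might infer earlier stopping on verum and hence bias in its favour. But 2.2 also says that these symptoms usually fade within days, 2.1 expects L-citrulline to avoid gastrointestinal effects, and the pilot had no drop-outs. No figure shows which arm would stop earlier, so the direction stays open.

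**Power.** A reader might infer that longer follow-up would raise power by keeping all 42 boys. That does not follow. The 10% loss may include consent withdrawal and relocation, carrying forward already keeps all 42 nominally, and outcomes measured off treatment may dilute the effect.

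**Laboratory wording.** Both sections can be true together: metformin must stop, and termination may follow. Reading 7.1 as requiring both abnormalities rests on one loosely used conjunction. That is fair, but the consequence and the fate of follow-up still differ on the page.

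**Conclusion.** The point holds as a design weakness. Sections 4.2.2 and 4.2.3 tie treatment-related events to leaving the study, no week-26 assessment is described afterwards, and 8.5 fills the gap with an earlier D1 value. The ITT analysis is undermined but not contradicted.

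The expected size is small: about 0.2 points on a 21-boy arm mean for each boy leaving at week 13, against a planned difference of about 11.2. It reaches about 0.8 points if all four expected losses leave one arm at week 13. These figures rest on a linear decline of 17.2 points per year and on the boys continuing to decline. Under those assumptions the arm that stops earlier is favoured; under others the sign can reverse.

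Nothing here shows the sample size to be wrong. The case for acting is that the imputation is avoidable and cheap to avoid. The difference between 4.2.2 and 7.1 is a separate matter of wording and consequence, and it must be reconciled.

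**What to change.** 1. In 4.2.2 and 4.2.3, distinguish stopping study medication from leaving the study. The investigator's safety ground for ending participation remains.
2. After medication is stopped or the code is broken, keep the scheduled week-13 and week-26 assessments (MFM, 6MWT, dynamometry, and MRI at week 26) where consent continues and the investigator sees no safety objection.
3. State in 8.5 and 8.6 that these measured values enter the ITT analysis in place of a carried-forward value.
4. The investigators should reconcile 4.2.2 and 7.1 so that trigger, force and consequence agree, including what happens to follow-up. The clinical content is theirs to decide.

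**Cost.** A short amendment, and a few already scheduled visits for boys who are off treatment. Their outcomes may dilute a treatment effect, which is part of what an ITT comparison measures.

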**4.2.3 Conditions for unblinding**

Unblinding is the process by which the allocation code is broken so that the investigator, clinical staff and/or the trial statistician becomes aware of the intervention for a person participating in a trial. The usual reason for unblinding is that a person participating in the study has encountered an urgent medical problem necessitating that the clinician know his/her intervention allocation. The principal investigator assess the need for unblinding where a serious adverse event has occurred and the treatment or allocation code is required in order to enable clinical treatments to

be planned. Upon unblinding, the site personnel will record the participant withdrawal and allocation in the person's clinical and trial notes along with the appropriate clinical notations.

**Unblinding envelopes:** A series of envelopes, each labelled with the randomisation number that contain the allocation for that person. These envelopes are sealed by the central randomisation service, and are only opened if emergency unblinding is required.

#### **4.3 Measure to minimise bias (randomising, blinding)**

Patients who meet the study admission criteria will be enrolled in the study and a single subject identification number will be assigned. Patients are allocated to the two study groups, L-citrulline and metformin or placebo, in a 1:1 ratio. The assigned number will be recorded in the CRF Visit 2. Drop outs after baseline visit (randomisation) will not be replaced.

The physiotherapists who perform the tests were trained and certified in Lyon where MFM has been established and validated.

This is a double blind, placebo controlled, randomized study.

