Due to the progressive nature of DMD MFM values and 2MWD decrease over time until free ambulation is lost (mean progression can be calculated based on data from the literature and correspond to predicted values (23, 24). In contrast, four of the five treated patients showed a marked improvement of their clinical and functional abilities. The mean total MFM (3,5%) and 2MWD (10 meter) improved. In addition, the MFM D1 subdomain (standing and transfers), which is the most informative dimension in ambulant DMD patients aged 6 years and over with a

mean decrease of 17.2% per year (23), improved by more than 6% in our treated DMD group. More importantly, this improvement is better than the maximal mean improvement reported for the total MFM and the D1 MFM subscore (both below 2%) after beginning a steroid treatment (standard symptomatic treatment of care)(25). Relevant changes observed in our trial are shown in table 2.

| Category    | Variable                  | mean  | median | SD   | range         | 95% CI         |
|-------------|---------------------------|-------|--------|------|---------------|----------------|
| calorimetry | REE, kcal/24 h            | -51.2 | -56.5  | 37   | -84 to -8     | -54 to -48.5   |
| calorimetry | carbohydrate oxidation, % | -17.9 | -11.3  | 18.4 | -44.8 to -4.4 | -20.7 to -15.1 |
| calorimetry | fatty acid oxidation, %   | 13.9  | 9.6    | 13.7 | 2.9 to 33.6   | 11.1 to 16.7   |
| Walking     | 2 min walking distance    | 9.58  | 9.6    | 29.3 | -40.3 to 30.6 | 6.8 to 12.4    |
| MFM         | total score, %            | 3.54  | 7.29   | 6.93 | -8.33 to 8.33 | 0.969 to 6.11  |
| MFM         | D1 subscore, %            | 6.15  | 7.69   | 11.6 | -12.8 to 15.4 | 3.58 to 8.72   |
| MFM         | D2 subscore, %            | 1.67  | 2.78   | 4.65 | -5.56 to 5.56 | -0.903 to 4.24 |
| MFM         | D3 subscore, %            | 1.91  | 0      | 5.43 | -4.76 to 9.53 | -0.665 to 4.48 |

Table 1: Descriptive statistics (mean, median, standard deviation, range, and 95% confidence interval) for selected variables of all five treated patients (change from baseline to post-treatment).

Individual and predicted (calculated using data from the literature (23,24)) MFM and the 2 min walking distance values of all treated patients are presented as follows:

[figure not shown]

Figure 2: Individual and predicted (calculated using data from the literature (23,24)) 2 min walking distance (A) and MFM (B) values of all treated patients.

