
DMD patients aged 4–17 years in the Italian cohort showed that the 6MWD performances increased (approximately 33 m/year) with age up to 7 years, with a clear point of slope change at approximately 7 years. After the age of 7 years, there was a variable decline in the 6MWT (-12 m/year) (24).

Secondary outcome measures:

- 2) Mean change of MFM total score, the D2, and D3 MFM subscores from baseline to week 26 under L-citrulline/metformin therapy compared to placebo (for details see 1)
- 3) Mean change of walking distance from baseline to week 26 under L-citrulline/metformin therapy compared to placebo assessed with the six-minute walk test (for details see 1)
- 4) Change of quantitative muscle MRI including muscle fat content (MFC) and T2 times of thigh muscles visualized by MRI (Magnetic Resonance Imaging) in both groups at week 26 versus baseline (for details see 2.2.2)
- 5) Change in the plasma / urine concentration for markers of muscle necrosis (resting creatine kinase, plasma), oxidative stress (8OHdG, urine; carbonylated proteins, 4-HNE, serum), nitrosative stress (nitrotyrosin, plasma; ADMA, serum; cGMP, urine), and change of miRNAs serum concentration in both groups at week 26 compared to baseline and compared to healthy controls.
- 6) Mean change of quantitative muscle force (QMT) of knee extension and elbow flexion using hand held dynamometry (HHD) from baseline to week 26 under L-citrulline/metformin therapy compared to placebo

Aims of our treatment are a stimulation of NO concentrations (indirect markers nitrotyrosine, ADMA and cGMP), an improvement of the muscular energy situation with reduction of oxidative stress (8OHdG, carbonylated proteins, 4-HNE as markers) and a slowing of the

muscle denegeration (creatine kinase as marker.) Aim of our treatment is a slowing of the natural history of the disease, so we plan to analyse possible serum biomarkers (miRNAs) of disease progression (26).

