### **5.2 Inclusion criteria**

- Molecular diagnosis of DMD

- Patients 6.5 - 10 years of age at time of screening
- Ambulant
- Ability to walk 150 m in the 6 min walking distance (6MWT)
- D1 subdomain of the MFM scale >40%
- stable treatment with steroids for >6 months or steroid naïve patients

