## **8.2 Planned number of trial subjects with clearly stated justification (possibly power analysis)**

For sample size estimation the MFM D1 subscore was chosen. Baseline and post-treatment measurements of 5 patients are available from the pilot study. A semi-parametric approach for sample size estimation was chosen that made use of these data. For the 2 min. walking distance, a mean change from baseline to post-treatment of 10 m was expected (estimated from pilot data). For the MFM D1 subscore, a mean change from baseline to post-treatment of 6.1 % was expected (estimated from pilot data). Sample size estimation was repeated for a range of values smaller and larger than the expected mean changes. Further, the influence of two randomisation ratios for the verum/placebo groups, 1:1 and 2:1, on sample size was checked. Each sample size,  $n_i=1, \dots, 40 = 11, \dots, 50$  for the MFM D1 subscore, was evaluated by drawing 99 times an individual data set of size  $n_i$  from the pilot study data set (sampling with replacement). In each of these individual data sets, each patient was randomly assigned to a verum or a placebo group. For each patient, the post-treatment value was

Version 8, 10.09.2015

calculated as the sum of the baseline value and a random variate drawn from a normal distribution with mean and standard deviation estimated from the pilot data. In the case of the placebo group, the mean was set to  $-17.2/54 \times 16$  for the MFM D1 subscore (value taken from Table 2 in (39)). (The values from the literature refer to changes within one year, i.e. 54 weeks, and the pilot study lasted 16 weeks, thus the linear transformation of the values by  $/ 54 \times 16$ .) For the primary endpoint candidate (MFM D1 subscore), assuming a drop-out rate of 10 %, a randomisation ratio of 1:1, and a power of 0.8, c. 42 patients should be recruited in order to be able to analyse 38 complete datasets. Fig. 4 shows how the sample size behaves with regard to the MFM D1 subscore, the power, and the randomisation ratio.

[figure not shown]

Fig. 4. Sample size with regard to the MFM D1 subscore and the power for a randomisation ratio of 1:1. The numbers on the curves indicate the power. The arrow shows how to interpret the plot. The curves are smoothed and only serve illustrative purposes.

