### **8.3 Description of the statistical methods foreseen and the planned intermediate assessments**

Non-parametric Wilcoxon signed rank test

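### The primary analysis uses no covariates or strata: baseline D1 (beyond its subtraction), steroid use and age are known before randomisation but left out, costing precision and not validity

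*Protocol*

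**What the plan says.** Section 4.3, on minimising bias, gives the allocation rule as "Patients are allocated to the two study groups, L-citrulline and metformin or placebo, in a 1:1 ratio". It names no stratification factor, block or minimisation scheme. Section 4.2.3 mentions a central randomisation service, also without factors.

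Section 8.3 gives the method in full as "Non-parametric Wilcoxon signed rank test". Section 8.1 defines the primary endpoint as the mean change in MFM D1 from baseline to week 26, compared with placebo.

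The eligible population is mixed on three characteristics (section 5.2):

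- **Steroid use:** "stable treatment with steroids for >6 months or steroid naïve patients".
- **Age:** 6.5 to 10 years.
- **Baseline D1:** any value above 40%.

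All three are known before randomisation. Age and steroid status are eligibility items, and the footnote to Table 2 makes the screening MFM the baseline value. Section 4.1 reports that the six-minute walking distance first rises and then falls with age, "with a clear point of slope change at approximately 7 years".

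Section 8.2 plans the size: "assuming a drop-out rate of 10 %, a randomisation ratio of 1:1, and a power of 0.8, c. 42 patients should be recruited". The number to be analysed after dropout is 38, which is 19 per arm.

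**The concern.** With about 19 boys per arm, the arms can differ by chance in steroid use, age or starting level. The protocol suggests that these factors may matter. It describes steroids as a standard treatment with an effect on the MFM. It places a change of walking-distance slope inside the eligible age range. It also says that how informative each MFM subscore is depends on disease stage.

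A test without covariates leaves whatever these factors explain in the error term. If the arms then look different at baseline, the single pre-specified result offers no adjusted estimate, and any later adjustment is post hoc. What is at stake is precision, and how convincingly a small trial can be read.

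**Working it through.** **1. Inputs.**

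- Active-arm change, section 8.2: "a mean change from baseline to post-treatment of 6.1 % was expected (estimated from pilot data"), so +6.1 points.
- Placebo-arm change, section 8.2: -17.2/54 x 16 = -5.10 points.
- Planned difference: 6.1 + 5.10 = 11.20 points.
- SD of the D1 change: 11.6, from the five-patient pilot table in section 3.1.1 (the row reads "11.6 | -12.8 to 15.4 | 3.58 to 8.72").
- Alpha 0.05 (section 8.4), taken as two-sided.
- 38 datasets at 1:1, so 19 per arm.

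**2. Reproducing the plan's figure.** A two-sample t-test needs 17.86 per arm. Dividing by the rank-test efficiency of 0.955 gives 18.7, so 19 per arm and 38 in all. A simulated rank-sum test with 19 per arm has power 0.80. For dropout, 42 x 0.9 = 37.8. The planned 38 and 42 therefore reproduce for a between-arm rank-sum test.

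**3. Chance imbalance in steroid use.** Let K of 42 boys take steroids and split them at random 21/21 (hypergeometric). The proportion is not in the protocol, so 40-70% is assumed, which is K = 17 to 29. A gap of 20 points means at least 0.20 x 21 = 4.2 boys. The gap in boys has the same parity as K, so this is 5 boys when K is odd and 6 when K is even. A gap of 30 points means at least 6.3 boys: 7 when K is odd, 8 when even.

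| K | P(gap at least 20 points) | P(gap at least 30 points) |
|---|---|---|
| odd, 17-29 | 18-22% | 4-6% |
| even, 18-28 | 10-12% | 2-3% |
| whole range | about 10-22% | about 2-6% |

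**4. What such a gap would do.** The protocol's only steroid figure for D1 is a mean improvement below 2% after starting treatment (section 3.1.1). A 20-point gap would shift the arm difference by less than 0.20 x 2 = 0.4 points, against the planned 11.20.

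**5. Power with and without adjustment.** Unadjusted t-test: SE = 11.6 x sqrt(2/19) = 3.76, and power is 0.825 on 36 degrees of freedom.

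Let k be the number of covariates and R their multiple correlation with the D1 change. Adjustment multiplies the variance by (1 - R²). It also adds a cost for chance covariate-treatment correlation, with expected factor 35/(35 - k) at N = 38, and uses k degrees of freedom. The protocol gives no R, so a range is shown. For k = 3 the factor is 35/32 = 1.094:

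| R (assumed) | Residual SD | SE | Power |
|---|---|---|---|
| 0 | 11.60 | 3.94 | 0.79 |
| 0.3 | 11.07 | 3.76 | 0.83 |
| 0.4 | 10.63 | 3.61 | 0.85 |
| 0.5 | 10.05 | 3.41 | 0.89 |

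The SE breaks even with the unadjusted one where (1 - R²) x 35/32 = 1, so R² = 3/35 and R = 0.29. For baseline D1 alone the factor is 35/34, so R² = 1/35 and R = 0.17, that is, near 0.2.

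**The case against.** Four objections have force.

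- **Baseline is already used.** A reader might infer that baseline D1 is ignored. It is not, because the endpoint is a change score. What remains is that subtraction fixes the slope on baseline at one, and any further dependence of change on starting level stays in the error.
- **Randomisation protects the test.** A reader might infer that an imbalance biases the trial, or could not be told from a drug effect. The documents do not support this. Randomisation keeps the comparison unbiased and the type I error controlled, and the one steroid figure implies a shift under 0.4 points. That figure describes starting steroids, not decline in stable users against naive boys, so it is only a guide. It is also silent on age and baseline D1.
- **The gain may be nil.** No passage correlates any of the three factors with D1 change, and the age evidence concerns walking distance, not D1. With three weak covariates, adjustment loses power. It would be wrong to call it free.
- **The protocol is silent on stratification.** It does not say that allocation is unstratified, and a randomisation specification may cover it. This stands for the design half of the point. It does not answer the analysis half: section 8.3 names the test, so a plan that used covariates would depart from the protocol.

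A signed rank test is also a paired test and does not compare two independent arms. That is a separate defect. It matters here only because section 8.3 has to be rewritten anyway.

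**Conclusion.** The point holds as a matter of efficiency and interpretability. The protocol fixes an analysis that cannot use steroid use, age or baseline level as covariates, in a trial of about 19 per arm where all three are in hand before randomisation. Validity is not in question.

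If about 40-70% of boys take steroids and allocation is unstratified, a gap of at least 20 points in steroid use has probability about 10-22%, and one of at least 30 points about 2-6%. Three-covariate adjustment changes power at the planned difference from 0.83 to between 0.79 (R = 0) and 0.89 (R = 0.5). It is neutral near R = 0.3 and helps only above that. Adjusting for baseline D1 alone pays from about R = 0.2. These power figures assume normal changes, the five-patient pilot SD and an R that the protocol does not supply.

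**What to change.** Rewrite section 8.3 so that the primary analysis is a between-arm ANCOVA, or rank ANCOVA if a non-parametric method is preferred, of D1 change at week 26 on arm and baseline D1. Pre-specify steroid use (yes/no) and age as further covariates. Adjust each secondary endpoint for its own baseline.

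State the randomisation method in section 4.3. If the list is still open, stratify it by steroid use; with about 40 boys, one factor, or at most two, is realistic.

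The analysis change needs no new data or visits. Its price is a little precision per covariate: about 0.04 of power with three covariates if they explain nothing (0.83 to 0.79), and about 0.01 with baseline D1 alone (0.825 to 0.813). If the sponsor doubts that age and steroid use predict D1 change, baseline D1 alone is the cautious choice. Stratifying needs a new randomisation list and is practical only before enrolment begins.
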